#### Psychological and nutritional status

The AD-EVA test inventory, an interdisciplinary test system for diagnosis and evaluation of obesity and other illnesses influenced by eating habits and motoric behaviour, as well as the Child Behaviour Checklist (CBCL/4-18) will be used to determine the psychological status of the participants. The CBCL is a widely used method to identifying problem behaviour in children [45], whereas the AD-EVA inventory is used to analyse psychological variables which are considered to cause or promote obesity [46]. The nutritional status will be assessed using the 24-hour recall method. This method records the daily, self-reported consumption of food-intake. In combination with a standardised nutritional food programme (EBISpro, Zurich, Switzerland) the intake of macronutrients and micronutrients will be estimated.

#### Adherence to the training programme

Intervention group participants will be asked to keep a day-by-day exercise log including adherence and average overall pain during and after each exercise session. The physiotherapist supervising the intervention programme will also monitor adherence to the group sessions. Adherence will be considered as the percentage of actually completed sessions during the intervention period among the number of intended exercise sessions. Studies investigating the feasibility of different exercise programmes for musculoskeletal disorders, which show good outcomes for patients, typically reported adherence percentages of greater than 80 % [26, 47, 48]. Therefore, we will a priori consider an adherence percentage of 85 % as feasible for our exercise programme. In addition, participants will be asked about their rating of change in knee-related well-being, pain and joint function using a 7-point ordinal scale.

### Sample size estimation

Primary outcome parameters for this study are the external frontal knee moment and impulse during walking. Recent studies have determined that a specific non-invasive training can facilitate a reduction of external knee adduction moment (EKAM) peaks of 13 % during stance [49]. In accordance with assumptions of Kean et al. [21], and the fact that EKAM impulse seems to be a more sensitive measure than peak EKAM [21], a magnitude of 5–10 % change in EKAM and external knee adduction moment impulse (EKAMI) seems to be achievable in this study. Based on our assumptions and the estimates of Kean et al. [21], we assume a medium to large effect size of *d* = 0.45. Based on a two-tailed repeated comparison of two groups (IG and CG) using one covariate (weight loss) for repeated analysis of covariance (ANCOVA), when the effect size is *d* = 0.45, power is 0.8, type I error is 0.05 and *df* = 1, the estimated total sample size is approximately 40. Allowing a dropout rate of approximately 20 % yields a total sample size of 48. Sample size was estimated using G*Power 3.1.3 [50, 51].

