### Study population

A total of 48 obese boys and girls aged between 10 and 18 years will be recruited for this study. Sample size estimation revealed that 48 participants is the minimum number which will guarantee that the study is not underpowered. Nevertheless, depending on time and other resources available, we will focus on achieving more than the planned sample size. Participants will be recruited from the community in metropolitan Vienna, Austria. For recruitment purposes the study will be advertised at an outpatient clinic for paediatrics. Participants will be eligible if the following inclusion criteria are met:Male or femaleAge: 10–18 yearsBody mass index (BMI) greater than the 97th percentile [25]Availability: can participate in two exercises session per week for a period of 12 weeks

Participants will be excluded if one or more of the following criteria are met:Present syndromes associated with obesity (e.g. Prader-Willi syndrome and similar disorders)Chronic joint diseases, osteoarthritis surgeryNeuro-motor diseases

All adverse and serious adverse reactions will be documented, monitored and participants will be discontinued based on the decision of the investigator.

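### The 20 % dropout allowance is calculated the wrong way round: keeping the stated 40 completers needs 50 enrolled, and 48 covers only about 17 % dropout (minor)

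*Protocol article*

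**What the plan says.** All the figures are in the protocol article.

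- **Sample size estimation, base number.** With "power is 0.8, type I error is 0.05", two-tailed testing, two groups, one covariate (weight loss) and an effect size of 0.45 labelled *d*, "the estimated total sample size is approximately 40".
- **Sample size estimation, dropout.** "Allowing a dropout rate of approximately 20" % then "yields a total sample size of 48".
- **Study population.** The same total becomes a firm claim: "48 participants is the minimum number which will guarantee that the study is not underpowered". The section adds that more participants will be sought if time and resources allow, without giving a number.
- **Abstract, Methods/Design.** It repeats 48 as the size of the trial.

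**The concern.** A dropout rate is the fraction of enrolled participants who are lost, so the number to enrol is the required number of completers divided by one minus that rate. Adding 20 % to the required number is a common slip, and it always falls short, because 20 % of the larger enrolled number is more than 20 % of the smaller required number.

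The base number, the dropout rate and the total are all printed here, and they disagree: if dropout occurs at the planned rate, the trial ends with fewer completers than the plan says it needs. At stake are a modest loss of power and the truth of the statement that 48 guarantees the trial is not underpowered.

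**Working it through.** **Inputs from the Sample size estimation section.** Two-sided alpha 0.05; power 0.80; two groups; numerator df = 1; one covariate; effect size 0.45; required total about 40; dropout about 20 %; enrolled total 48. Equal allocation is assumed, because the ratio is not stated.

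**1. Reproducing the 48.**
40 × (1 + 0.20) = 48. The match is exact.

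**2. The allowance that 20 % dropout requires.**
Enrolled = completers / (1 − dropout) = 40 / 0.80 = 50.

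**3. What 48 delivers.**
- Completers at 20 % dropout: 48 × 0.80 = 38.4, about 38.
- Highest dropout that still leaves 40: 1 − 40/48 = 16.7 %.
- Shortfall in the enrolled total: 50 − 48 = 2 participants.

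**4. Settings that reproduce the base of about 40.** The G*Power settings are not shown, so this step rests on assumptions. Two readings give a minimum of 41, close enough to the stated figure:
- *Reading A:* ANCOVA, one covariate, 0.45 entered as Cohen's f. Noncentrality λ = f² × N = 0.2025 × N, denominator df = N − 3.
- *Reading B:* group-by-time interaction, d = 0.45 (f = 0.225), two time points, assumed pre-post correlation 0.5. λ = f² × N × 2 / (1 − 0.5) = 0.050625 × 4 × N = 0.2025 × N, denominator df = N − 2.

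The noncentrality is the same in both, so the choice between them hardly affects power.

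**5. Power from the noncentral F distribution** (probability that F with noncentrality λ exceeds the central 95 % point):

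| Completers | λ | Power, reading A | Power, reading B |
|---|---|---|---|
| 38 | 7.695 | 0.770 | 0.770 |
| 40 | 8.100 | 0.791 | 0.792 |
| 41 | 8.3025 | 0.802 | 0.802 |

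**6. Splitting the shortfall.** From 40 to 38 completers, power falls from 0.79 to 0.77, about 2.2 percentage points. That part comes from the dropout arithmetic. The further gap of just under 1 point between 0.79 and 0.80 comes from rounding the base number and exists before any dropout.

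**7. Sensitivity to the assumed correlation (reading B).** Power at 38 completers would be 0.69 at a correlation of 0.4, 0.77 at 0.5 and 0.85 at 0.6. The required number would be 49, 41 and 34 respectively. Of these, only 0.5 is consistent with the stated base of about 40.

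**The case against.** **Both inputs are approximate.** The section hedges the 40 and the 20 %, and a gap of two participants is within what such wording might cover. This limits the importance of the point but does not remove it. The total equals 40 × 1.20 exactly, which points to the formula and not to rounding, and the Study population section drops the hedge when it calls 48 a guaranteed minimum.

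**The team hopes to recruit more than 48.** If it does, the shortfall may disappear. The intention depends on resources and fixes no number, so it mitigates the consequence without making the stated figure right.

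**Intention-to-treat analysis.** One could argue that dropouts stay in the analysis. However, the planned repeated measures ANCOVA uses follow-up values and weight change, and a participant lost before follow-up has neither observed. The section's own dropout allowance treats such participants as lost to the power calculation.

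**Stronger readings that the document does not support.**
- A reader might infer that power collapses to about 0.27 at 38 completers, because the effect size is labelled *d* and a plain between-group comparison with d = 0.45 gives that value. The section specifies a repeated comparison, and d = 0.45 with two time points and a correlation of 0.5 gives 0.77. How the effect size is labelled is a separate question from the dropout arithmetic.
- A reader might take f = 0.45 as the plan's own input. The document writes *d*; f is a reconstruction that happens to reproduce the base number.
- A reader might conclude that 52 must be enrolled (41 / 0.80 = 51.25). The 41 rests on settings that are not shown. The printed figures support only 40 to 50.

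**Conclusion.** The point holds as a minor arithmetic error. From the printed figures alone, 20 % dropout needs 50 enrolled, 48 leaves about 38 completers, and 48 is sufficient only up to 16.7 % dropout. None of this depends on an assumption about the test.

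The cost in power is about 2 percentage points against the stated base of 40 and about 3 against the nominal 0.80. That size rests on equal allocation and on settings that reproduce the base of about 40; under another pre-post correlation the power would differ, but the base number would then differ too. The claim that 48 guarantees adequate power is not true at the plan's own dropout rate. The error does not threaten the design.

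**What to change.** **Preferred: keep 48 and correct the wording.**
- In Sample size estimation, state that 48 enrolled allows for about 17 % dropout. Alternatively, keep 20 % and state that it leaves about 38 completers and about 77 % power, naming the assumption used (0.45 as Cohen's f, or d = 0.45 with two time points and a pre-post correlation of 0.5).
- In Study population, replace the guarantee with a statement conditional on the assumed effect size and dropout.
- The Abstract needs no change, since it gives only the total.

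**Alternative: change the target.** Set the total at 50 and update Sample size estimation, Study population and the Abstract to match.

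The first route costs a sentence in each of two sections. The second costs two more participants, which fits the stated wish to recruit beyond 48.

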## Discussion

This study will attempt to evaluate a 12-week strength training and neuromuscular exercise programme for obese children from a biomechanical and clinical perspective. Effects on biomechanical gait characteristics during level walking and stair climbing will be analysed. Up to date only a few interventional studies exist: e.g. [22], which have analysed the impact of a training programme on gait during level walking of obese participants. This study aims at extending current research as well as adding analyses of changes in biomechanical gait characteristics during stair ascent and descent.

The main aspects of the programme focus on strengthening quadriceps and hip muscles in combination with neuromuscular exercises. The training programme aims at developing a more neutral alignment of the trunk and lower limbs during locomotion, thereby intending to improve the position of the knee in relation to the hip and the ankle joints. It may, therefore, enhance activation of muscle groups generating internal moments which counteract external moments in the frontal plane of the knee. The training programme will follow state of the art recommendations in musculoskeletal rehabilitation [27–29] and intends to motivate children and adolescents to exercise regularly, due to its specifically adjusted and attractive design for the age group in question. Further, only cost-effective equipment will be used, thus increasing its feasibility in common physiotherapy practices.

A single assessor-blinded, pre-test and post-test randomised controlled trial design will be utilised to investigate any biomechanical and clinical changes that may occur due to the intervention programme. The primary biomechanical outcome parameters in this study will be the overall peak external frontal knee moment normalised for BW × HT (Nm/(BW × HT)%) and the impulse. These parameters are well-accepted surrogate measures for knee joint loading [20]. Kutzner et al. [20] reported a high correlation between the tibio-femoral force measured by an instrumented knee implant and the EKAM (*R*^2^ = 0.76), suggesting that EKAM is well-suited to predict the medial tibio-femoral contact force, particularly during the early stance phase. Even though EKAM is a well-accepted measure for knee joint loading, concerns have recently emerged stating that peak EKAM only measures the load at one instance of stance and does not reflect joint loading over the entire stance phase [21]. Although peak moments can be reduced through slower walking speed, the increased duration of stance phase and, therefore, the time under load can result in an overall increase of joint loading. For this reason the impulse (e.g. external knee adduction moment impulse) has been demonstrated to provide a more comprehensive measure [21] as it takes into account both the magnitude of load and the duration of stance.

Clinical outcomes comprise the KOOS questionnaire, measures of self-reported pain during and after each training session and adherence to the training programme. In detail the KOOS questionnaire will assess participants’ knee pain and other symptoms, function in daily living (ADL), function in sport and recreation (Sport/Rec) and knee-related quality of life (QOL). In addition, the training programme will be evaluated from a clinical perspective by including the following analysis: cardiopulmonary testing to quantify aerobic fitness effects as well as anthropometric measures, nutritional and psychological status.

The primary findings of this study will help to determine whether a neuromuscular and strengthening exercise programme for an obese population of children can reduce joint loading during locomotion, and thus decrease the possible risk of developing degenerative joint diseases in adulthood.

## Trial status

The ethics committee has approved the study protocol. Participant recruitment will start at the end of September 2015 and it is anticipated that the necessary number of participants will be tested until the beginning of 2017. Data analysis will be conducted subsequently.

## Consent

Written informed consent was obtained from the patient(s) for publication of this manuscript and accompanying images. A copy of the written consent is available for review by the editor-in-chief of this journal.

## Abbreviations

3D: three-dimensiona
ADL: function in daily living (KOOS)
AP: anterior pituitary hormone
ANCOVA: analysis of covariance
AT: anaerobic threshold
BCM: body cell mass
BMI: body mass index
BW: body weight
CBCL/4-18: Child Behaviour Checklist
CG: control group
CONSORT: Consolidated Standards of Research Trials
ECM: extracellular mass
EKAM: external knee adduction moment
EKAMI: external knee adduction moment impulse
FFM: free fat mass
FM: fat mass
GH: growth hormone
HT: height
IG: intervention group
IGFBP: insulin-like growth factor binding protein
IL: interleukin
IR: interquartile range
ITT: intention-to-treat
KOOS: Knee injury and Osteoarthritis Outcome Score
LBM: lean body mass
P: maximum power
PP: per protocol
pVO_2_: peak oxygen consumption
QOL: quality of life (KOOS)
RPE: rated perceived exertion
SD: standard deviation
Sport/Rec: function in sport and recreation (KOOS)
TBW: total body water
VT2: ventilatory threshold
TGF-α: transforming growth factor alpha
